#### Safety assessment index

The following information will be recorded/measured for the safety assessment; vital signs, general medical examinations, renal function tests, liver function tests and adverse events.

### Procedures

#### Recruitment

Participants will be recruited on a voluntary basis from a cohort of patients with pre-diabetes attending Nawaloka Hospitals PLC, Colombo, Sri Lanka. Informed written consent will be obtained from all study participants.

#### Study schedule

Fasting blood glucose, 2-h OGTT blood glucose, serum insulin, the liver profile (AST, ALT, PT/INR) and the renal profile (blood urea and serum creatinine) will be measured at the 0,1, 3 and 6 months. In addition, the serum lipid profile (total cholesterol, triglycerides, LDL cholesterol, HDL cholesterol) and serum HbA_1_c would be measured at baseline, at 3 months and on completion of the study. The details of items which will be measured at every visit are described in Fig. 1.

### Measurement tools

#### Anthropometric measurements

Height will be measured using Harpenden pocket stadiometers (Chasmors Ltd, London, UK) to the nearest 0.1 cm. Body weight will be measured in indoor light clothing to the nearest 0 .1 kg using a SALTER 920 digital weighing scale (Salter Ltd, Tonbridge, UK). Waist circumference will be measured midway between the iliac crest and the lower rib margin at the end of normal expiration using a plastic flexible tape to the nearest 0 .1 cm. Similarly, the hip circumference will be measured at the widest part of the buttocks in the inter-trochantric level to the nearest 0 .1 cm. All anthropometric measurements will be made by trained personnel. All anthropometric measurements (height, weight, BMI, WC, HC and WHR) will be made using standard calibrated equipment and following recommended guidelines [28]. The equipment used for anthropometric measurements will be calibrated by the Department of Measurement Units, Standards and Services, Colombo, Sri Lanka [29].

#### Dietary measurements

A culturally validated Food Frequency Questionnaire (FFQ) will be used to obtain habitual intake of calories, macronutrients and micronutrients [30]. The FFQ contains color photographs of three different portion sizes of four commonly consumed foods (rice, green vegetable curry, lentil curry and chicken) and a list of food items (*n* = 85) with their portion sizes and frequencies. Each respondent is expected to report consumption of each food according to frequency. Food items are categorized into eight food groups, namely: cereals; vegetables; pulses; meat; fruits; drinks; miscellaneous; and alcohol. The FFQ is interviewer-administered in the local language (Sinhalese and Tamil). The participants will be asked to recall their usual portion size and intake of foods listed within the FFQ over the past month. FFQ data will subsequently be analyzed and be reported as the intake of calories, carbohydrates, fat, proteins and dietary fibers per day. Furthermore, intake of lysine, vitamin C and zinc will also be analyzed.

#### Physical activity

Physical activity during the past week will be assessed using the translated and validated short version of the International Physical Activity Questionnaire (IPAQ) administered by an interviewer and will be presented as energy expenditure expressed in metabolic equivalent (MET) minutes/week [31]. The continuous score allows the estimation of the weekly energy expenditure expressed in MET minutes/week. This is obtained by multiplying the value of energy expenditure for the given physical activity in MET by the weekly frequency (days per week) and the time in minutes (minutes per day). These values are separately computed for the three domains of walking, moderate-intensity activities and vigorous-intensity activities using the following formulas:$$ \mathrm{Walking}\ \mathrm{MET}\ \mathrm{minutes}/\mathrm{week}=3.3\times \mathrm{minutes}\times \mathrm{days}, $$$$ \mathrm{Moderate}\ \mathrm{MET}\ \mathrm{minutes}/\mathrm{week}=4.0\times \mathrm{minutes}\times \mathrm{days}, $$$$ \mathrm{Vigorous}\ \mathrm{MET}\ \mathrm{minutes}/\mathrm{week}=8.0\times \mathrm{minutes}\times \mathrm{days}. $$

A combined total physical activity MET minutes/week can be computed as the sum of these three domains.

#### Biochemical analysis

Centrifuged serum separated samples (2200–2500 rpm) will be used for the assays. The glucose assay will be performed by an enzymatic colorimetric (glucose oxidase) method in an RxDaytona™ chemical analyzer (Randox Laboratories Ltd, Antrim, UK). Total cholesterol and LDL cholesterol will be analyzed by an enzymatic colorimetric method in a Mindray BA-88A semi auto-analyzer (Mindray Medical International Ltd, China). HDL cholesterol will be determined by a precipitation method in a Mindray BA-88A semi auto-analyzer. Triglyceride will be analyzed by an enzymatic colorimetric method in a Mindray BA-88A semi auto-analyzer using commercially available enzymatic colorimetric determination kits for triglycerides.

#### Clinical examination

Seated blood pressure will be recorded on two occasions after at least a 10-min rest using an Accoson mercury sphygmomanometer (Accoson Healthcare, Asia-Pacific Region, Singapore).

#### Other

In addition to the aforementioned sociodemographic data, drugs and data on side effects would also be gathered via a questionnaire.

### Compliance calculation

Subjects will be asked to return remaining drugs and their compliance will be evaluated using the following formula:$$ \mathrm{Compliance}\ \left(\%\right)=\left[\left(\mathrm{distributed}\ \mathrm{drugs}-\mathrm{remaining}\ \mathrm{drugs}\right)/\mathrm{distributed}\ \mathrm{drugs}\right]\times 100. $$

### Statistical analysis

Parametric and nonparametric statistical tests will be applied using SPSS version 16 (SPSS Inc., Chicago, IL, USA) and Stata/SE 10.0 (Stata Corporation, College Station, TX, USA) for data analysis. FFQ data will be analyzed using NutriSurvey 2007 (EBISpro, Germany), nutrient analysis software for Windows, modified for Sri Lankan food items and recipes, and will be reported as the intake of calories, carbohydrates, fat, proteins and dietary fibers per day. Summary statistics will be calculated and presented as mean, standard deviation and proportion by group. The baseline and end of study characteristics as well as the laboratory findings of the groups will be compared using two-sample and paired *t* test, and *P* < 0.05 will be considered significant. The Homeostasis Model Assessment (HOMA2) calculator will be used to calculate β-cell function (HOMA-β) and insulin resistance (HOMA-IR) based on fasting insulin and plasma glucose [32]. The Homeostatic Model Assessment (HOMA) is a method used to quantify insulin resistance and β-cell function. It has good correlation with the traditional, invasive and time-consuming euglycemic clamp method (*r* = 0.88) which is used to measure insulin resistance and β-cell function.

Multiple regression analyses will be performed, where change in FPG/OGTT/HbA1c post intervention from baseline are the continuous dependent variables and independent variables will be age (continuous), treatment group (0, placebo; 1, Lysulin™), gender (0, female; 1, male), physical activity (continuous), BMI (continuous), energy intake (continuous), carbohydrate intake (continuous) and baseline FPG/OGTT/HbA1c. All analyses will follow intention-to-treat principles and a prespecified analysis plan. Where appropriate, sensitivity analyses will be conducted (e.g., control for additional covariates; and bootstrapped *P* values for skewed outcomes). In the case of missing data values, we will apply mean imputation and regression imputation where rates are low, and consider multiple imputations where they exceed 10%.

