### Objectives and hypothesis

#### Hypotheses

Primary—the glycemic control of people with pre-diabetes who are treated with Lysulin™ tablets will be better than that of the control group.Secondary—progression to diabetes would be reduced and other related metabolic parameters (serum insulin, total cholesterol, triglyceride, HDL cholesterol, LDL cholesterol and blood pressure) will be improved in the treatment group in comparison to the control group.

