#### Objectives

Primary—to evaluate the potential effects of Lysulin™ tablet supplementation on glycemic control and disease progression in patients with pre-diabetes.Secondary—to evaluate effects on serum lipids, anthropometric parameters, blood pressure and appetite, and also to study potential effects of regular administration of Lysulin™ tablets on liver and kidney function and the occurrence of self-reported side effects in patients with pre-diabetes.

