### Outcomes

#### Primary outcome index

The primary outcome will be defined as the change in glycemic control measured by HbA1c from baseline.

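### The article names two-sample t tests, within-arm paired t tests and a baseline-adjusted regression for HbA1c without saying which decides the primary outcome; a paired test cannot answer the between-arm hypothesis

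*Protocol article*

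**What the plan says.** **Question.** The primary hypothesis (Hypotheses) is that glycemic control on Lysulin "tablets will be better than that of the control group". The Sample size section is built on a 0.5% HbA1c difference between the two groups. Both are between-arm statements.

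**Outcome.** Under Primary outcome index: "The primary outcome will be defined as the change in glycemic control measured by HbA1c from baseline". That sentence gives neither a visit nor a test. The Study schedule has HbA1c at baseline, 3 months and completion.

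**Analysis.** The Statistical analysis section states: "The baseline and end of study characteristics as well as the laboratory findings of the groups will be compared using two-sample and paired" t tests, followed by the section's only threshold, P "< 0.05 will be considered significant". Laboratory findings include HbA1c. The next paragraph plans multiple regression in which "change in FPG/OGTT/HbA1c post intervention from baseline are the continuous dependent variables". The covariates are treatment group, age, gender, physical activity, BMI, energy intake, carbohydrate intake and the baseline value. The same section says: "All analyses will follow intention-to-treat principles and a prespecified analysis plan". That plan is not among the documents shown.

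**Objectives.** The primary objective covers effects on "glycemic control and disease progression in patients with pre-diabetes". The Hypotheses and Secondary outcomes sections both make progression to diabetes secondary.

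**The concern.** Three kinds of analysis are named for the primary outcome and none is given precedence. It is also unclear whether the two-sample test is on end values or on change.

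The paired test is the more serious part. The two arms are independent groups, so a paired t test can only compare baseline with end of study inside one arm. It says nothing about Lysulin against placebo, yet it shares a sentence and a significance threshold with the between-arm test. Under Interventions, both arms get the same diet and activity advice, so HbA1c may fall in both without any drug effect. A report that the active arm improved significantly and the placebo arm did not would then look like evidence of efficacy without being a treatment comparison.

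Leaving the choice among between-arm tests open has a smaller cost: the chance that at least one is significant exceeds the nominal 5%.

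**Working it through.** **1. The plan's own figure.** From Sample size: E = 0.5, S = 0.82, q1 = q2 = 0.5, z values 1.96 and 0.84, drop-out 20%.

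N = (1/0.5 + 1/0.5) × (1.96 + 0.84)² / (0.5/0.82)² = 4 × 7.84 / 0.3718 = 84.3. This is 42.2 per arm, rounded up to 43, or 86 in total. 86 / (1 − 0.20) = 107.5, rounded up to 108. The stated 108 is reproduced, and it is a between-arm calculation. With 55 randomized per arm and 20% lost, 44 per arm complete. The steps below use n = 44.

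**2. Paired tests when both arms drift equally and the drug does nothing.** Let δ be the common drift in units of the SD of change (assumed; the article gives no such figure). The paired t statistic has 43 degrees of freedom and noncentrality δ√44. Let p be the chance that it is significant in the direction of improvement. The arms are independent, so the pattern 'active significant, placebo not' has probability p(1 − p).

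| δ | δ√44 | p | p(1 − p) |
|---|---|---|---|
| 0.2 | 1.33 | 0.25 | 0.19 |
| 0.3 | 1.99 | 0.49 | 0.25 |
| 0.4 | 2.65 | 0.74 | 0.19 |

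To put δ in HbA1c units: the SD of change is 0.82 × √(2(1 − ρ)), where ρ is the baseline-to-end correlation. At ρ = 0.5 this is 0.82, so δ = 0.2 to 0.4 is a fall of 0.16% to 0.33% HbA1c in both arms.

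A simulation in raw units (20,000 trials per scenario, SD 0.82, ρ = 0.5 to 0.7, equal falls of 0.1% to 0.3%) gave 10% to 25% for the same pattern.

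**3. Choosing among between-arm tests, no drug effect.** Simulated bivariate normal HbA1c, 44 per arm, ρ assumed to be 0.3 to 0.7:

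| What may count as the primary test | Chance of at least one P < 0.05 (two-sided) |
|---|---|
| Any one test, named in advance | about 5% |
| Change t test or baseline-adjusted regression | about 6.5% to 8% |
| Those two or an end-value t test | about 9% to 10% |

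The tests are positively correlated, so the last row is below the 1 − 0.95³ = 14.3% that three independent tests would give.

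**4. Precision.** Standardized effect 0.5/0.82 = 0.61. For the unadjusted end-value t test with 44 per arm, power is 81%. Adjusting for baseline multiplies the residual SD by √(1 − ρ²). At ρ = 0.5 this is 0.866, the standardized effect becomes 0.61/0.866 = 0.70, and power is 90%.

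**5. Objectives against outcomes.** Objectives: disease progression is part of the primary objective. Hypotheses: progression is secondary. Primary outcome index: HbA1c change only. Secondary outcomes: development of diabetes is listed. Three sections agree and the Objectives section does not.

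**The case against.** The strongest reply is that this is a condensed article which refers to a prespecified analysis plan. The choice of the deciding model commonly sits in that plan, and its absence from an article is not a fault. Everything else about the primary question is between-arm, and no sentence says that a paired result will support an efficacy claim. This reply stands in part, and it is why the point is a should-fix. It does not remove the point, because the article goes beyond silence: it states a within-arm test beside the between-arm test, with the same threshold. That sentence needs correcting whatever the plan says.

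Several stronger readings are tempting, and the documents do not support them:

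- **All tests are declared at P < 0.05.** The threshold is written only in the t test sentence. It is the only one in the section, but it is not attached to the regression.
- **Discordant paired tests mislead in 38% to 50% of trials.** That is 2p(1 − p), which counts either arm. Half of those trials are significant on placebo only and give no false claim for Lysulin.
- **The primary type I error is 9% to 10%.** That requires admitting an end-value test, although the outcome is defined as change. A false result in favour of Lysulin arises in about half of those trials.
- **Three glycemic endpoints inflate the primary error to 11% to 14%.** FPG and OGTT are declared secondary. Sharing a regression sentence with HbA1c does not make them co-primary.
- **Regression to the mean makes both arms improve.** Entry may be on fasting or 2-h glucose alone, and the HbA1c band is bounded above at 6.4%. The direction and size for HbA1c cannot be derived from the article.
- **The precision of baseline HbA1c is thrown away.** The regression already includes it. The gain is lost only if the unadjusted test is the one that decides.

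**Conclusion.** The point holds in this form. The article names several analyses of HbA1c, does not say which one decides, and gives equal standing to a paired test that cannot address the between-arm hypothesis.

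If paired results were used as evidence, the misleading pattern favouring Lysulin would appear in about 19% to 25% of null trials. This rests on an assumed equal drift of 0.2 to 0.4 SD of change, which the shared lifestyle advice makes plausible but which the article does not quantify. Free choice between the change t test and the regression costs little (about 6.5% to 8% against 5%), and somewhat more if an end-value test is admitted (about 9% to 10%). Both ranges assume a baseline correlation of 0.3 to 0.7. The 90% against 81% power comparison assumes a correlation of 0.5.

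The mismatch over disease progression is a separate wording inconsistency and does not depend on any of these assumptions. The sample size is unaffected. Severity: should-fix.

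**What to change.** In Statistical analysis:

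- Name one primary analysis: the planned between-arm regression of 6-month HbA1c change on treatment, with baseline HbA1c, age and sex as covariates. Report the adjusted difference with its 95% CI, tested two-sided at 0.05. Age group and sex are the stratification factors under Randomization. The model with BMI, physical activity, energy and carbohydrate intake added can be kept as a sensitivity analysis, which the section already allows for.
- Make the unadjusted two-sample test supportive, and say whether it is on end values or on change. Label the FPG and OGTT regressions secondary.
- Limit within-arm paired comparisons and baseline comparisons between arms to description.

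In Objectives, move disease progression to the secondary objectives, to match Hypotheses and Secondary outcomes.

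If the unshown analysis plan already names the primary test, bring the protocol text into line with it.

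**Cost.** Wording only. The regression and its covariates are already planned, N stays at 110, no data are added, and the Trial status section says that enrollment has not begun.

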### Randomization

Randomization for the parallel treatment arms will be carried out after checking the inclusion and exclusion criteria. The patients will be randomized in a 1:1 ratio according to the method of block randomization with a block size of 4. The population will be stratified at randomization based on age (< 30 years and ≥ 30 years) and gender to ensure equal distribution of these variables in the two arms. The randomization sequence would be generated using the SPSS statistical software package (version 14.0). Concealment of the allocation sequences will be done using sequentially numbered, opaque, sealed, color-coded envelopes. Eligibility assessment and enrolment will be done by one independent investigator, while another investigator will be involved in randomization. The investigator involved in randomization shall open the next respective color-coded envelope depending on the stratification and allocate the patient to the respective group (treatment or control). The treatment and control groups shall be designated as either ‘A’ or ‘B’ and this allocation shall be kept in a sealed envelope in a secure place during the course of the study. The manufacturer will be responsible for preparing the study medications designated either ‘A’ or ‘B’.

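### Randomisation is stratified by gender and age group, but the only between-arm test named for the continuous non-glycaemic secondary outcomes is an unadjusted t test, which is conservative and loses power if applied to end-of-study values

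*Protocol article*

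**What the plan says.** The Randomization section of the protocol article fixes the design: "The population will be stratified at randomization based on age (< 30 years and ≥ 30 years) and gender". Allocation is in small blocks: "The patients will be randomized in a 1:1 ratio according to the method of block randomization with a block size of 4". Envelopes are opened according to stratum, so near-balance of the arms is forced within each of the four gender-by-age cells.

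The Statistical analysis section names two kinds of analysis:

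- A general comparison: "The baseline and end of study characteristics as well as the laboratory findings of the groups will be compared using two-sample and paired" t tests, at P < 0.05. The paired test is within arm, so the two-sample test is the between-arm comparison. It carries no stratum term.
- A multiple regression, "where change in FPG/OGTT/HbA1c post intervention from baseline are the continuous dependent variables and independent variables will be age (continuous), treatment group", then "gender (0, female; 1, male), physical activity (continuous), BMI (continuous), energy intake (continuous), carbohydrate intake (continuous") and the baseline value of the glycaemic variable. It covers three variables only.

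The Secondary outcomes section also lists lipids, HOMA indices, anthropometry and blood pressure, each as change from baseline. Serum insulin appears in the secondary hypothesis. None of these has a regression. Control for further covariates is mentioned only as a possible sensitivity analysis.

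**The concern.** Stratified blocks take the between-stratum variation out of the true sampling error of the arm difference, because both arms contain nearly the same mix of men, women and age groups. A pooled t test still counts that variation in its standard error. If gender or age group predicts the outcome, the reported interval is wider and the P value larger than the design warrants.

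What is at stake is precision on the secondary hypotheses, with about 88 completers expected. Raw end-of-study weight, waist, hip, waist:hip ratio and HDL are the plausible places for a material gender difference. The general sentence in Statistical analysis speaks of end-of-study characteristics, so as worded it points to those raw values.

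**Working it through.** **Size of the trial.** From the Sample size section: difference 0.5, SD 0.82, critical values 1.96 and 0.84, 20% drop-out. The stated formula gives 4 × (1.96 + 0.84)² / (0.5/0.82)² = 84.3 in total, or 42.2 per arm, rounded up to 43. Then 43/0.8 = 53.75, rounded up to 54 per arm, which is the stated 108. With 110 recruited, 110 × 0.8 = 88 complete, 44 per arm.

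**Assumption.** The article does not say how much outcome variance gender and age group explain. Call this share R² and take a range.

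**End-of-study values, closed form.** Work in SD units and assume exact balance within strata.

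- Standard error the t test reports: √(1/44 + 1/44) = 0.213.
- True standard error: 0.213 × √(1 − R²). The reported one is too wide by 1/√(1 − R²).
- The t test rejects beyond 1.988 × 0.2132 = 0.424.
- Type I error: 2Φ(−0.424 / true SE).
- Power at 0.4 SD: t test Φ((0.4 − 0.424) / true SE); strata-adjusted model Φ(0.4 / true SE − 1.989).

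| R² | True SE | SE too wide by | Type I error, t test | Power, t test | Power, adjusted | Points lost |
|---|---|---|---|---|---|---|
| 0.05 | 0.208 | 2.6% | 4.1% | 45% | 47% | 2 |
| 0.10 | 0.202 | 5.4% | 3.6% | 45% | 50% | 4 |
| 0.20 | 0.191 | 11.8% | 2.6% | 45% | 54% | 9 |
| 0.40 | 0.165 | 29.1% | 1.0% | 44% | 67% | 22 |

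**End-of-study values, simulated.** Incomplete blocks and drop-out leave the balance imperfect, so simulation gives a slightly milder picture. With 88 completers at R² 0.1, 0.2 and 0.4, type I error of the t test is about 4%, 3–4% and 1.5–2%. The power lost at 0.4 SD is about 4–5, 8 and 22 points. A separate run (20,000 trials per setting, half men and 15% under 30 assumed) at 0.5/0.82 = 0.61 SD gives these powers, t test against adjusted:

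- R² 0: 80.4% against 80.3%
- R² 0.05: 81.5% against 82.8%
- R² 0.10: 81.8% against 84.5%
- R² 0.20: 83.3% against 88.6%
- R² 0.40: 86.1% against 95.5%

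The adjusted model stays between 4.9% and 5.3% type I error throughout.

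**Change from baseline.** Write the baseline value as m + e₀ and the final value as m + e₁ + arm effect, where m is the stratum mean. If m is the same at both times, the change is e₁ − e₀ + arm effect: m cancels and the strata explain none of it. Simulation agrees. With end-value R² of 0.2 or 0.4 and within-stratum correlation of 0.5, 0.8 or 0.9 (assumed), a plain t test on change has type I error of 4.2–5.6%. Adding strata moves its power by at most 0.5 points. If strata do explain 5–10% of the change itself, the loss is about 1–3 points at 0.5 to 0.61 SD of the change.

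**Role of the baseline value.** At correlation 0.8 and 0.4 SD, end-of-study values adjusted for strata alone have 54% power (R² 0.2) and 66% (R² 0.4). A simple t test on change has 90% and 96%. With the baseline value in the model, adding strata takes power from 92% to 92% and from 97% to 98% at correlation 0.8. At correlation 0.3 it goes from 54% to 58% and from 62% to 70%.

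**The case against.** The strongest reply is that the Secondary outcomes section defines these outcomes as changes from baseline. A stable difference between men and women then cancels, and the mismatch costs almost nothing. This stands, and it rules out the reading that most secondary outcomes lose 10 or 20 points of power. It does not remove the point, because the Statistical analysis sentence describes a comparison of end-of-study characteristics and nowhere says that the t test is run on change.

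Second, the baseline value matters more than the strata when end values are analysed. This also stands, and it shapes the fix.

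Third, a reader might infer that every between-arm test outside the regression ignores the strata, or that the P values are invalid. The article supports neither. It also allows unnamed nonparametric tests ("Parametric and nonparametric statistical tests will be applied using SPSS version 16"), names no test for development of diabetes, and permits covariate control as a sensitivity analysis. The error is in the conservative direction only.

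Fourth, the article refers to a prespecified analysis plan that is not shown, and the choice of covariates for secondary models often sits there. That would carry weight if the article were silent. It names a specific test, and that test does not match its own randomisation.

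Finally, no secondary outcome is powered in the Sample size section, so the effect sizes used here are illustrations, not planned targets.

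**Conclusion.** The point holds in a limited form. For lipids, insulin/HOMA, blood pressure and anthropometry, the one between-arm test named takes no account of the factors by which the trial randomises.

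- On end-of-study values the test is conservative: type I error of about 4% down to 1.5%, and about 4 to 22 power points lost at 0.4 SD, for an assumed R² of 0.1 to 0.4.
- On change from baseline the loss is near zero if gender and age differences are constant over time, and about 1 to 3 points (at 0.5 to 0.61 SD) if strata explain 5–10% of the change.
- If the strata explain nothing, nothing is lost.

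The treatment estimate is not biased and false positives are not inflated. The primary HbA1c regression already contains gender, age and baseline. This is a loss of efficiency worth correcting because the correction is almost free; it does not threaten the trial's validity. All sizes rest on the assumed R², 88 completers and drop-out unrelated to outcome.

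**What to change.** In Statistical analysis, for the post-baseline between-arm comparisons of the continuous secondary outcomes outside the glycaemic regression, replace the two-sample t test with the linear model form already used for FPG, OGTT and HbA1c. It should contain at least treatment arm, gender, age (continuous or as the randomisation stratum) and the outcome's own baseline value. Strata without the baseline value would be a poor substitute, as the figures above show. The baseline comparisons should be left out of this change. If the analysis plan already specifies such a model, the sentence only needs to be brought into line with it.

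The cost is one sentence and about three degrees of freedom (86 to 83 with 88 completers). Gender and age are already used at randomisation and baseline values are already collected, so no new data are needed. Trial status says enrolment has not started, so the change can be made before any outcome is seen.

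### The only between-arm comparison stated for laboratory findings is a t test on means, which is insensitive to large liver or kidney abnormalities in one to three of 55 participants

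*Protocol article*

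**What the plan says.** Under Objectives, the protocol article sets as a secondary aim "to study potential effects of regular administration of Lysulin™ tablets on liver and kidney function". The Safety assessment index lists "renal function tests, liver function tests and adverse events" among what will be recorded. Under Study schedule, the liver profile (AST, ALT, PT/INR) and the renal profile are frequent: urea and "serum creatinine) will be measured at the 0,1, 3 and 6 months".

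For analysis, the Statistical analysis section first allows a general toolkit: "Parametric and nonparametric statistical tests will be applied using SPSS version 16" and Stata, with no test tied to a variable. It then says "Summary statistics will be calculated and presented as mean, standard deviation and proportion by group", without defining a proportion for any laboratory test. The one sentence that assigns a comparison to laboratory values says that baseline and end-of-study characteristics, "as well as the laboratory findings of the groups will be compared using two-sample and paired" t tests, and P "< 0.05 will be considered significant". The regression models that follow cover only FPG, OGTT glucose and HbA1c.

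Individual patients are dealt with elsewhere. Suspension criteria include serious adverse events and unusual changes in test results. Adverse effect evaluation provides for recording of adverse events and their review by a Data Safety Monitoring Board.

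**The concern.** A liver or kidney effect of a supplement may appear as a small shift in everyone or as a marked rise in a few people. A comparison of means is suited to the first pattern. In the second, each extreme value raises the mean a little and the SD a lot, so the test statistic stays small. Beyond a point, more extreme values make significance less likely.

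Two further features of the plan could hide such a pattern. If the laboratory comparison is confined to baseline and end of study, a rise at month 1 or 3 that has settled by month 6 does not enter it. And if a participant is suspended for abnormal results and the month 6 value is missing, the general missing-data rule (mean or regression imputation where rates are low), if applied to these tests, would put a typical value in place of an atypical one.

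At stake is the answer to a stated secondary objective. A table of means with P values above 0.05 could sit beside several marked elevations in the active arm without showing them, although the samples that would show them are already scheduled.

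**Working it through.** **The plan's own figure.** The protocol gives no number for liver or kidney safety. Its only sample size is for HbA1c: 2 × (1.96 + 0.84)² × 0.82² / 0.5² = 42.2, so 43 per arm and 86 in total; 86 / 0.8 = 107.5, rounded up to the stated 108 and recruited as 110. That fixes the arm sizes used here: 55 randomized per arm, or 55 × 0.8 = 44 after the planned 20% drop-out.

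**Hand illustration.** Assumptions not in the documents: ALT SD 15 U/L in both arms; 2 of 55 treated participants raised by 175 U/L at the visit compared; none on placebo.
- Shift in mean: 2 × 175 / 55 = 6.4 U/L.
- SD in the treated arm: √(15² + 175² × (2/55) × (53/55)) = 36.0, up from 15.
- Standard error: √(36.0²/55 + 15²/55) = 5.26.
- t = 6.36 / 5.26 = 1.21; with about 72 Welch degrees of freedom, two-sided P is about 0.23.
- If both values have settled by the visit compared, the expected difference is zero.

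**Simulation over a range.** Assumptions not in the documents: lognormal ALT with mean 25 U/L and coefficient of variation 40%, baseline to follow-up correlation 0.7, ULN 40 U/L. In each trial k treated participants are set to a multiple of ULN at follow-up and none on placebo; 8,000 trials per setting. Entries are the percentage of trials with two-sided P < 0.05 for the two-sample t test at follow-up / the two-sample t test on change / the paired t test within the treated arm, with 55 per arm.

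| k of 55 | 3 × ULN | 5 × ULN | 10 × ULN |
|---|---|---|---|
| 1 | 4.1 / 3.6 / 1.6 | 1.6 / 0.7 / 0.0 | 0.0 / 0.0 / 0.0 |
| 2 | 8.4 / 7.8 / 4.7 | 4.4 / 2.7 / 0.5 | 0.2 / 0.0 / 0.0 |
| 3 | 18.3 / 18.9 / 16.1 | 18.2 / 15.2 / 8.4 | 7.5 / 4.1 / 0.5 |
| 4 | 36.2 / 39.5 / 43.1 | 49.5 / 53.7 / 56.0 | 65.2 / 70.6 / 72.0 |
| 5 | 58.6 / 67.3 / 78.8 | 82.9 / 89.8 / 96.4 | 99.3 / 99.9 / 100 |

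With 44 per arm the pattern is the same: at 5 × ULN, k = 2 gives 3.8 / 2.0 / 0.3 and k = 3 gives 16.9 / 14.6 / 6.6.

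With one to three affected participants, the chance of significance falls as the elevation grows from 3 to 10 × ULN. With one or two at 5 × ULN or more, it is below the nominal 5%.

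**Would a test on counts do better?** Not as a significance test. Fisher's exact test with 55 per arm gives P = 0.50 for 2 v 0, 0.24 for 3 v 0, 0.12 for 4 v 0, 0.057 for 5 v 0 and 0.027 for 6 v 0. The gain from counting is that the events and their uncertainty become visible. For 2 of 55 (3.6%) the exact 95% interval runs from 0.4% to 12.5%. For 0 of 55 its upper limit is 1 − 0.025^(1/55) = 6.5%.

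**The case against.** The strongest reply is that this is an omission, not an error. Exceedance counts and shift tables are usual content of an analysis plan; the article refers to a prespecified one that is not at hand, and a journal article need not list such tables. That stands: their absence is not the finding. The finding is that the article does state a method for laboratory findings, and that the stated method is insensitive to a pattern that matters for a stated objective.

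Several stronger readings are tempting, and the documents do not support them.
- *That safety is judged by t tests.* The sentence names no liver or renal test; applying it to them is an inference, though a natural one because no other comparison is given. Suspension for unusual results, adverse event recording and safety-board review are separate routes by which a marked rise could come to light. They protect individuals, but the board's stated task is adverse events, no stated rule makes a symptom-free laboratory rise an adverse event, and none of these routes yields a stated comparison between arms.
- *That t tests cannot show such elevations.* At 5 × ULN they reach significance in about half of trials with four of 55 affected and in most trials with five.
- *That month 1 and month 3 rises are certainly lost.* The reference to baseline and end of study attaches grammatically to the characteristics and may not limit the laboratory findings. Nothing says that interim values go unanalysed.
- *That P > 0.05 will be reported as no effect.* No section says so.

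It is also fair to say that much of the insensitivity comes from the sample size, since Fisher's test on 2 v 0 is no more significant. This is why the remedy is a descriptive table with intervals and not a different test. Finally, the protocol expects minor events because the ingredients lie within recommended allowances. That bears on how likely the pattern is, not on whether the stated analysis would show it.

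**Conclusion.** The point holds in limited form. T tests on means are the only between-group comparison stated for laboratory findings. If they are applied to the liver and renal tests, they will seldom be significant when one to three of 55 treated participants have large elevations: under 5% of trials for two at 5 × ULN, and 8 to 18% for three. Sensitivity is about even for four at that level and good for five. At 3 × ULN it is lower, with 36 to 43% for four and 59 to 79% for five. Transient rises are missed in addition only if the comparison is confined to end of study.

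These figures rest on assumed ALT distributions, on no elevations in the placebo arm, and on the reading that laboratory findings include the safety tests. The pattern was the same at 3, 5 and 10 × ULN and at 44 and 55 per arm. The matter deserves a change because the data are already scheduled and Trial status says that enrolment has not started, so reporting limits can be set before any results are seen.

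**What to change.** In the Statistical analysis section, state separately how the liver and renal tests will be reported:
- For AST, ALT, PT/INR, urea and creatinine, take each participant's worst post-baseline value over all visits, including values before withdrawal, with no imputation.
- Report by arm the number and proportion whose worst value exceeds prespecified laboratory limits, with exact confidence intervals and the number of participants with at least one post-baseline value as denominator. These are limits for reporting only and set no rule for patient management.
- Add a baseline-to-worst shift table by arm.
- Keep means and SDs by visit as description.
- State that a non-significant t test will not be interpreted as evidence of no liver or kidney effect.

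If the analysis plan already contains these tables, a cross-reference and the last statement are enough.

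The cost is one extra table and some wording; no new samples are needed. The intervals will be wide at this sample size (an upper limit of 6.5% even with no events in 55), so the table will describe what was seen and will not establish safety.
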